## Methods/design

### Setting

This study is part of the Alpe d’HuZes Cancer Rehabilitation (A-CaRe) programme, which includes multiple projects with two main purposes (1) to evaluate the (cost-) effectiveness of rehabilitation programmes for cancer patients, A-CaRe 1 [88–95], and (2) to implement these programmes in daily patient care, A-Care 2 [96–100]. Our study concerns the A-Care 2 programme. The Committee on Research Involving Human Subjects of the region Arnhem-Nijmegen of the Netherlands assessed the study and concluded that our study will be carried out in accordance with the applicable rules concerning the review of research ethics committees and informed consent.

### Design

This study is a clustered controlled before and after study (CBA).

It will compare a patient-directed strategy with a multi-faceted strategy to implement evidenced-based PCRPs. We consider PCRPs evidence based, when the features of the programme are in line with the recommendations of the evidence-based Dutch guidelines (‘Cancer Rehabilitation’ , and ‘Cancer Survivorship Care’) and additional international literature and guidelines [19, 22, 23, 29, 101].

For the selection, development and testing of the implementation strategies, we will follow a stepwise and structured approach, summarized in Fig. 1, based on the Grol and Wensing implementation of change model [81].

**Fig. 1. Fig1:**
[figure not shown]
Overview of the planned stepwise approach of the study

In *step 1*, we will first analyse the currently achieved implementation of PCRPs in daily care and examine the factors (barriers and facilitators) that might influence optimal implementation of PCRPs. In *step 2*, we will use the background information of step 1 and a literature study to develop and tailor implementation strategies to the target group, the setting and the barriers to change. In *step 3*, we will then compare newly achieved implementation with the implementation measurements from step 1 to assess and compare the effectiveness of the two implementation strategies by a CBA design. We will also conduct a process evaluation and cost analysis. Clustering of the CBA study will be on the hospital level as matched pairs in a 1:1 ratio. The hospitals are situated in different regions in the Netherlands, and hospitals will be stratified by the study group, according to type of hospital (university, teaching and non-teaching hospitals) and capacity (number of beds).

Each group will contain one university, two teaching and two non-teaching hospitals in the Netherlands.

During our study, healthcare professionals of the participating hospitals will hand out patient information and informed consent to all eligible patients. Patients that give informed consent will be approached, screened and if eligible included as participant for one or more analyses of our study.

Professionals are asked for participation by writing. Professionals that give informed consent will be screened and if eligible included as a professional participant for one or more analyses of our study.

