##### Study population

Structure indicators will be collected from the 10 participating hospitals, and process and outcome indicator data will be collected from 500 adult cancer patients in the participating hospitals (about 50 adult patients per hospital). The group of patients included are patients with preferably (a history of) cancer located in the gastro-intestinal, reproductive and/or urological systems and that have successfully passed their primary treatment without signs of recurrence or metastases.

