The results of the literature search will, together with the knowledge based on the results of the preparatory phase in step 1, be the basis to select and develop the implementation strategies during roundtable discussions. For the five hospitals of the PD-strategy group, a single-faceted patient-directed strategy will be designed that will embed the change only at the patient level. For the hospitals of the MF-strategy group, a multi-faceted strategy will be designed that will embed the change at the patient, professional and organizational levels. The MF strategy will consist also of the PD strategy, so the additional value of the strategies directed at the professional and organization can be evaluated afterwards. For the roundtable discussions, an expert panel will be composed consisting of representatives from the participating hospitals (patients, healthcare professionals and hospital managers), experts on cancer rehabilitation and experts on implementation science.

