### Step 3: testing phase

The designed implementation strategies will be used to deploy the PCRPs in daily care and will be evaluated and compared on (A) effectiveness, (B) experiences of participants (process evaluation) and (C) costs. In all participating hospitals, the trial will be conducted for a half to 1 year, depending on the number of cancer patients per year in the participating hospitals allowing for fast accrual. Between 6 to 12 months after introduction of the implementation strategies, the outcomes of the PD and MF strategies will be evaluated and compared.

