##### Data collection

As described in the ‘Analysis of the currently achieved implementation of PCRPs in daily care’ section, quality indicators will be used to explore the actual achieved implementation of the PCRPs after the introduction of the developed implementation strategies. By comparing the implementation of PCRPs before and during the implementation period, we can evaluate the effectiveness of the strategies. The process of data collection of the quality indicators during the implementation period will be similar as the pre-measurement described in the ‘Analysis of the currently achieved implementation of PCRPs in daily care’ section.

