##### Study outcomes

The primary outcome measures are two quality indicators: (A) the percentage of screened patients with the screening tool recommended by the Dutch guideline ‘Cancer Rehabilitation’ and (B) the percentage of referrals to PCRPs where needed, according to the Dutch guideline ‘Cancer Rehabilitation’.

Secondary outcome measures are the differences in adherence between the pre- and post-measurement to the remaining quality indicators (process and structure indicators) extracted from the Dutch guideline ‘Cancer Rehabilitation’ and often-used outcome indicators as QoL and patient empowerment.

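### Entry to both primary percentages runs through handout by professionals whom only the multi-faceted strategy targets, and the post-period population is not tied to exposure, so selection that changes in one arm or unexposed patients can distort the contrast

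*Protocol article*

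**What the plan says.** All places are in the protocol article.

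- **Recruitment** (Methods/design, Design, text after Fig. 1): "healthcare professionals of the participating hospitals will hand out patient information and informed consent to all eligible patients". It continues: "Patients that give informed consent will be approached, screened and if eligible included as participant for one or more analyses of our study".
- **Who is targeted** (Step 2): for the MF hospitals, "a multi-faceted strategy will be designed that will embed the change at the patient, professional and organizational levels". The PD strategy works on patients only. Hospitals are allocated without randomization.
- **Primary outcomes** (Step 3, Study outcomes): "the percentage of screened patients with the screening tool recommended by the Dutch guideline" and "the percentage of referrals to PCRPs where needed".
- **Population** (Step 1, Study population): about 50 adults per hospital, preferably with a current or past cancer at the named sites, "that have successfully passed their primary treatment without signs of recurrence or metastases". Step 3 gives the post-measurement population the same characteristics.
- **Timing** (Step 3, opening paragraph): "the trial will be conducted for a half to 1 year, depending on the number of cancer patients per year in the participating hospitals", with evaluation between 6 and 12 months after introduction. Step 3, Data collection, compares implementation "before and during the implementation period".
- **Safeguards:** process and outcome indicators come from existing registration systems where available. Patient characteristics are included as possible confounders. The pre-post differences are compared between arms. Hospitals are matched 1:1 and stratified by type and number of beds.

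**The concern.** Each primary percentage has a denominator made up of patients who were handed papers by hospital staff and then consented. In one arm those staff are a target of the intervention, and they cannot be unaware of it. The strategy starts between the two measurements, so the way patients reach the study may change in the MF arm and not in the PD arm. If enrolment is related to having been screened or referred, the recorded percentage moves although care has not.

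The stated safeguards do not reach this. Record-based indicators limit measurement error but not the choice of who is measured. Adjustment for age, stage or therapy does not correct selection on the outcome itself. The limitations paragraph of the Discussion covers lack of randomization, local initiatives and hospital motivation, but not selection of patients within hospitals.

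The second issue is exposure. The post-period population repeats the baseline definition, and a past cancer with primary treatment completed is enough. A patient whose opportunity for screening fell before the strategy was introduced therefore meets the definition, and would pull the post-period percentage back towards its old level.

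**Working it through.** **Inputs from the article:** 50 % (MF) against 20 % (PD), 5 hospitals per arm, 50 patients per hospital, 10 % dropout (45 evaluable per hospital, 225 per arm), two-sided alpha 0.05, power 0.80.

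**Assumptions (no figure in the article):** enrolment ratio r, share unexposed u, intracluster correlation (ICC).

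**1. The plan's sample size.** Without clustering, 50 % against 20 % needs 39 evaluable patients per arm. The planned 225 corresponds to a design effect of 225/39 = 5.77, that is an ICC of (5.77 − 1)/44 = 0.108. The stated size is thus compatible with its inputs at an ICC near 0.11 under the normal approximation. Since the ICC is not given, the power figures below are shown at 0.05, 0.08 and 0.11.

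**2. Selection that changes in one arm.** If patients with the outcome are r times as likely to enrol as those without, the recorded rate is p·r/(p·r + 1 − p). For a true 20 %, with selection only in the MF post-period:

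| r | Recorded rate | Shift (points) |
|---|---|---|
| 1.25 | 0.25/1.05 = 23.8 % | 3.8 |
| 1.5 | 0.30/1.10 = 27.3 % | 7.3 |
| 2 | 0.40/1.20 = 33.3 % | 13.3 |

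In the opposite direction, if patients *without* the outcome become 1.25 times as likely to enrol in the MF post-period, a true 50 % is recorded as 0.50/(0.50 + 0.625) = 44.4 %, a loss of 5.6 points.

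**3. Selection constant over time.** With r = 2 in both periods and no true change from 20 %, the recorded pre-post difference is 33.3 − 33.3 = 0. With a true change from 20 % to 50 % it is 66.7 − 33.3 = 33.3 points instead of 30. The cancellation is large but not exact.

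**4. Unexposed patients.** If a share u of post-period patients in both arms is unexposed and stays at 20 %, the difference is 30·(1 − u). At u = 0.20 it is 24 points, 44 % against 20 %.

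Power uses a noncentral t with 8 degrees of freedom for a comparison of post-period percentages, with SE = √{[p₁(1 − p₁) + p₂(1 − p₂)]·[1 + 44·ICC]/225}. At ICC 0.08 the design effect is 1 + 44·0.08 = 4.52:

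- 50 against 20: SE = √(0.41·4.52/225) = 0.0908, noncentrality 0.30/0.0908 = 3.31, power 0.82.
- 44 against 20: SE = √(0.4064·4.52/225) = 0.0904, noncentrality 0.24/0.0904 = 2.66, power 0.64.

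| ICC | Power, all exposed | Power, 20 % unexposed |
|---|---|---|
| 0.05 | 0.93 | 0.79 |
| 0.08 | 0.82 | 0.64 |
| 0.11 | 0.72 | 0.54 |

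**The case against.** The strongest reply is that the article plans for *all* eligible patients to receive the papers, so a bias needs staff to fall short of that, or consent to depend on having been screened. This limits the size. If every screened patient and 80 % of the unscreened receive the papers, r is 1/0.8 = 1.25 and a true 20 % reads as 23.8 %. A ratio of 2 means that at most half of the unscreened receive them. The reply does not remove the risk, because the consent step remains.

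A reader might infer four stronger points that the article does not support:

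- **That the bias favours MF.** The MF elements are not yet designed. MF staff who hand out papers more completely could lower the recorded MF rate relative to PD.
- **That a 13-point false difference is to be expected.** It needs r = 2 in one arm and one period only. The article compares pre-post differences, in which constant selection largely cancels.
- **That the timing statements conflict.** Evaluation at 6 to 12 months fits within an implementation period of a half to 1 year.
- **That the volume-dependent window biases the arms.** Matching on type and beds should roughly balance window length. What remains is some mixing of exposure times, mainly in the exploratory comparison by hospital type.

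It is also fair to say that an article leaves sampling details and calendar windows to the full protocol. The point therefore rests on what the article does fix: the handout route, and a post-period population defined exactly as at baseline.

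**Conclusion.** The concern holds in two limited parts.

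First, the recruitment route allows selection to change between the two measurements in one arm, and neither record-based ascertainment nor case-mix adjustment would correct it. At assumed ratios of 1.25 to 2 for a true 20 %, the shift is about 4 to 13 points against a planned 30. Its direction is unknown, and a larger sample does not reduce it.

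Second, the reused population definition can admit unexposed patients after introduction. If they are 20 % of the post-period sample in both arms, the effect falls to 24 points and power drops by 0.14 to 0.18 over ICCs of 0.05 to 0.11. The 20 % is illustrative, and the power figures refer to a comparison of post-period percentages, not to the full pre-post contrast.

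This warrants an inexpensive improvement to sampling. It does not show that the design is invalid. The variable window is a minor matter.

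**What to change.** In both periods, identify consecutive eligible patients from the hospital registration lists and invite all of them in order until about 50 per hospital are included. Send the invitation in the hospital's name under the approved consent procedure, so that it does not depend on the discretion of the treating professional. The article does not show that the research team may contact patients before they consent, so the hospital should remain the sender.

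Count as post-period only patients who completed primary treatment after the strategy was introduced in their hospital, and use a matching window before introduction for the baseline. Report the numbers listed, invited and consenting per arm and period, so that a change in selection can be seen.

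Outcomes, arms and sample size stay as they are. According to the Trial status section, no indicator data had been gathered at submission, so at that stage both measurements could still follow the new procedure. The cost is some list and mailing work, and slower accrual in low-volume hospitals.

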### Step 1: preparatory phase

#### Analysis of the currently achieved implementation of PCRPs in daily care

Quality indicators will be used to explore the actual implementation of the PCRPs.

##### Study population

Structure indicators will be collected from the 10 participating hospitals, and process and outcome indicator data will be collected from 500 adult cancer patients in the participating hospitals (about 50 adult patients per hospital). The group of patients included are patients with preferably (a history of) cancer located in the gastro-intestinal, reproductive and/or urological systems and that have successfully passed their primary treatment without signs of recurrence or metastases.

##### Data collection

The quality indicators will be developed by a panel of 10–12 professional experts and patients, using the RAND-modified Delphi method [102, 103]. These indicators will be developed to measure the success of implementation and adherence to the recommendations of the Dutch guideline ‘Cancer Rehabilitation’ . With these extracted quality indicators (structure, process and outcome) and frequently used outcome indicators as QoL and patient empowerment, actual performance of the current implementation of PCRPs will be measured in the participating 10 hospitals. Data about adherence to the structure quality indicators will be collected consulting a panel consisting of healthcare professionals, management and patients from the 10 participating hospitals. Data about adherence to the processes and outcome quality indicators will be retrieved retrospectively from existing registration systems. Data not available will be surveyed by questionnaires. For example, to measure the outcome indicators QoL and patient empowerment, we will use the European Organisation for Research and Treatment of Cancer Quality of life Questionnaire-C30 (QLQ-C30) and the Patient Activity Measure (PAM) questionnaire.

We will also collect data about patient characteristics such as age, cancer type, clinical stage, co-morbidity, performance status and types of therapy to find possible confounding factors.

All indicators will be measured, using a data extraction form. A data extraction form will also be developed and pilot tested to register patient characteristics and other aspects relevant to assess the extent of implementation.

##### Planned analytic approach and outcomes

The main outcome measure is the adherence to quality indicators (process and structure indicators) from the PCRPs and their implementation (for example, outcomes of the QLQ-C30 and the PAM questionnaires).

In this measurement, adherence to the quality indicators will be used as dependent variables and patient characteristics (e.g. age, cancer type, clinical stage, co-morbidity, performance status and types of therapy) will be included as possible confounders.

#### Examine the factors (barriers and facilitators) for successful implementation of PCRPs

The qualitative study will be based on focus-group interviews and individual interviews.

##### Study population

The participants invited for the focus groups and individual interviews will be recruited from the 10 hospitals that are participating in our study.

The focus-group interviews concern the following groups: (a) four groups of 10–12 adult patients with preferably (a history of) cancer located in the gastro-intestinal, reproductive and/or urological systems, receiving treatment with curative intent or that have successfully passed their primary treatment. (b) Four groups of 10–12 professionals involved in the treatment of these cancer patients in secondary care (e.g. surgeons, radiotherapists, medical oncologists, gynaecologist, urologist, rehabilitation physicians, sports-medicine physicians, physical therapists, physician assistants and psychologists).

Additional to the focus-group interviews, we will conduct individual interviews with 30–40 professionals involved in the treatment of cancer patients in primary care (e.g. general practitioners, physical therapists and psychologists).

##### Data collection

The outcomes of the qualitative study will be collected through a semi-structured interview process. Four interview guides (one for patients, one for professionals involved in the secondary care, one for general practitioners and one for physical therapists and psychologists) will be developed using theoretical models developed by Cabana [104] and Grol [77] for identification of influencing factors. These models have four similar domains: characteristics of the innovation itself, characteristics of professionals, characteristics of patients and characteristics of the organization and context in which the innovation has to be applied. All interviews will be audio recorded and verbatim written in a document.

Besides the factors collected during the interviews, we will collect the characteristics of the participants of the interviews. Patients are asked to fill in a form that states their age, sex, home setting, working situation, cancer type and types of therapy. Professionals are asked to fill in a form that states their age, sex, years of practice, function and speciality.

##### Planned analytic approach and outcomes

The barriers and facilitators mentioned in the interviews will be independently qualitatively analysed by two researchers, using the qualitative software package Atlas.ti version 7 and will be descriptive. The factors identified will be classified within the framework that has been developed by Cabana [104] and Grol [77]. Factors identified, but not present in the models, will be added. The two sets of scores from the two researchers will be compared, and any discrepancies will be discussed until consensus is achieved. This approach will provide barriers and facilitators on different levels, including features of the PCRPs, the group of professionals involved in the care, group of patients and organization and context in which the PCRPs have to be applied.

### Step 2: selection and development phase

We will select and develop two implementation strategies to implement the PCRPs. We will create: A single-faceted patient-directed (PD) strategy that will embed the change at the patient level.A multi-faceted (MF) strategy that will embed the change at the patient, professional and organizational levels. It will also consist of the same patient-directed elements as the PD strategy.

Hospitals are requested for participation in our study by an invitation letter that will be sent by e-mail or post, and after agreement, they will receive full information for participation through a presentation. Interested hospitals will then meet with the study personnel (e.g. project manager, senior researcher and junior research fellow) in order to reach a clear understanding of all study components and to provide written informed consent. After inclusion, the hospitals will be allocated to either the PD- or MF-strategy group, taking into account sufficiently comparable settings and organizations in both the PD- and MF-strategy groups. In the Netherlands, cancers of the gastro-intestinal, reproductive and urological systems account for more than 35 % of the incidence of all cancers, being more than twice the incidence of breast cancer. Until now, however, most cancer rehabilitation programmes are designed and focused on breast cancer. Patients with gastro-intestinal and gynaecological cancers judge their cancer care low in comparison with patients with other tumour types. [55]. Patients with gastro-intestinal cancers also rated the information after finishing the primary treatment significantly lower in comparison with breast cancer patients [105]. Therefore, we choose to focus on cancer patients and their healthcare professionals in the care pathways for gastro-intestinal, gynaecological and urological oncology.

To develop the PD and MF strategies to deploy cancer rehabilitation programme(s), a literature search will be done. This literature search will be performed in MEDLINE, Embase and CINAHL, to define the evidence of implementation strategies for PCRPs. The search will be limited to studies of human beings and will have an English language restriction. The search terms will include the methodological filters of the 'Cochrane EPOC (Effective Practice and Organisation of Care) group' combined with selected MeSH terms and free-text terms. We will also use the snowball method for inclusion of further relevant trials.

Inclusion criteria are as follows:Population:Adult cancer patients andHealthcare workers involved in their care

We will not include studies in non-adult populations because of the differences in medical decision-making regarding children and adolescents, including the parents/guardian role.2.Intervention:

Strategies aimed at improving exercise during and after cancer. We define implementation as any planned process and systematic introduction of guidelines, healthcare innovations or health behaviour, aiming to be given a structural place in the patient’s life and professional practice.

We consider any of the strategies detailed in section 2 ‘Interventions’ of the 'EPOC Data Collection Checklist 2002':Professional interventionsFinancial interventionsOrganizational interventionsRegulatory interventions

In the 'EPOC Data Collection Checklist 2002', interventions focused on patients are categorized under financial and organizational interventions. Since we believe that nowadays interventions focused on patients are an important part of implementation strategies, we decided to add the category patient interventions to the list of ‘Interventions’ . We decided to use the following subjections under the category patient interventions, related to the subjection of the category professional interventions:Distribution of educational materialsEducational meetingsLocal consensus processesEducational outreach visitsLocal opinion leaders (in this category, healthcare professionals)Patient-mediated interventionsAudit and feedbackRemindersMarketing andMass media

We will include any active or passive implementation strategy. The combination of two or more strategies will also be considered as a valid intervention. Both studies describing implementation strategies alone or additionally to PCRPs will be included.3.Comparison:Outcomes before the introduction of the rehabilitation programme or strategy orOutcome comparison groupi.Where another programme orii.Control: no programme or usual care was implemented4.Type of outcome:All outcomes of ‘type of targeted behaviour’ section 2.3 of the 'EPOC Data Collection Checklist 2002'

The results of the literature search will, together with the knowledge based on the results of the preparatory phase in step 1, be the basis to select and develop the implementation strategies during roundtable discussions. For the five hospitals of the PD-strategy group, a single-faceted patient-directed strategy will be designed that will embed the change only at the patient level. For the hospitals of the MF-strategy group, a multi-faceted strategy will be designed that will embed the change at the patient, professional and organizational levels. The MF strategy will consist also of the PD strategy, so the additional value of the strategies directed at the professional and organization can be evaluated afterwards. For the roundtable discussions, an expert panel will be composed consisting of representatives from the participating hospitals (patients, healthcare professionals and hospital managers), experts on cancer rehabilitation and experts on implementation science.

